
**Fig 2 pone.0350084.g002:**
[figure not shown]
Primary diagnostic workup of patients with ATTR amyloidosis at the ACCB. Baseline examinations after diagnosis (left) as well as additional examinations depending on organ manifestation (right) are depicted for each specialty. NIS, neuropathy impairment score; FAP stage, family amyloid neuropathy stage, NCS, nerve conduction studies; EMG, electromyography, SEP, sensory evoked potentials; MRI, magnetic resonance imaging; CSF, cerebrospinal fluid examination; MEP, motor evoked potentials; VEP, visual evoked potentials; GOT, aspartate aminotransferase; GPT, glutamate pyruvate alanine aminotransferase; GGT, gamma-glutamyl transferase; CBC, complete blood count; TSH, Thyroid Stimulating Hormone; IgG, immunoglobulin G; IgA, immunoglobulin A; IgM, immunoglobulin M; CK, creatine kinase; Vit B12, vitamin b12; Vit A, vitamin A; HbA1c, glycated hemoglobin; NTproBNP, N-terminal pro B-type natriuretic peptide; NYHA, New York Heart Association heart failure stage; ECG, electrocardiogram; DPD, 99mTc-3,3-diphosphono-1,2-propanodicarboxylic acid; CMR, cardiac magnetic resonance imaging; VUS, variant of unknown significance.

### Baseline data collection AL amyloidosis

Patients with AL amyloidosis always present to hematology and cardiology outpatient clinics. As depicted in Fig 3, we include structured medical history, laboratory testing, urine testing, and whole-body-CT scan for detection of osteolysis. Whenever an underlying malignancy is suspected, bone marrow aspirates and biopsies including histology, cytology, flow cytometry and cytogenetics are performed. Since systemic AL-amyloidosis often affects the heart [9], cardiological screening is always performed, including NYHA stage, ECG, echocardiography, DPD-scintigraphy. For confirmation of AL-amyloidosis, a histologic confirmation of the subtype is mandatory. Therefore, a biopsy of an affected organ is performed if histologic confirmation is lacking [10]. Depending on organ manifestations suspected clinically or during laboratory screening, neurological, nephrological, or gastroenterological data is collected by the according specialist.

**Fig 3 pone.0350084.g003:**
[figure not shown]
Primary diagnostic workup of patients with (suspected) AL amyloidosis at the ACCB. Examinations after diagnosis (left) as well as additional examinations depending on organ manifestation (right) are depicted for each specialty. Abbreviations: NTproBNP, N-terminal pro B-type natriuretic peptide; GOT, aspartate aminotransferase; GPT, glutamate pyruvate alanine aminotransferase; GGT, gamma-glutamyl transferase; CBC, complete blood count; TSH, Thyroid Stimulating Hormone; IgG, immunoglobulin G; IgA, immunoglobulin A; IgM, immunoglobulin M; CK, creatine kinase; Vit B12, vitamin b12; HbA1c, glycated hemoglobin; osteo-CT, quantitative computed tomography; FISH, fluorescent in situ hybridization; NYHA, New York Heart Association heart failure stage; ECG, electrocardiogram; DPD, 99mTc-3,3-diphosphono-1,2-propanodicarboxylic acid; CMR, cardiac magnetic resonance imaging.

### Baseline data collection AA amyloidosis

AA amyloidosis is caused by the extracellular deposition of serum amyloid A (AA) protein, typically in the context of chronic inflammation due to autoimmune, autoinflammatory, infectious, or neoplastic condition [11]. In addition, recent studies suggest that gain-of-function mutations in the *SAA* promoter region may represent a genetic contributor to disease susceptibility and progression [12]. Patients most commonly present to nephrology with nephrotic-range proteinuria and/or impaired kidney function [13]. Medical history focuses on underlying rheumatological disease (autoimmune or autoinflammatory), gastrointestinal symptoms, genetic background, and other potential etiologies such as chronic infections or immunodeficiencies. The diagnosis of AA amyloidosis is confirmed by histological detection of AA amyloid deposits. Selection of the biopsy site is guided by the affected organ and the invasiveness of the procedure. In case of proteinuria or impaired kidney function, a kidney biopsy is recommended to confirm the diagnosis and exclude alternative treatable renal diseases.[14]. Systemic organ involvement should be assessed clinically and through laboratory testing as summarised in Fig 4. Proteinuria is often the earliest and most readily detectable manifestation of AA amyloidosis, reflecting renal involvement. However, systemic organ involvement is common, with frequent involvement of the gastrointestinal tract (including liver and spleen), the peripheral nervous system (e.g., neuropathy), and the heart (e.g., restrictive cardiomyopathy) [15]. Baseline data is collected from all organ system suspected to be involved during baseline screening in the rheumatological outpatient clinic.

**Fig 4 pone.0350084.g004:**
[figure not shown]
Baseline diagnostic workup of patients with (suspected) AA amyloidosis at the ACCB. Examinations are depicted depending on data type (left) and specialties involved (right). CRP, c-reactive protein; PCT, procalcitonin; IL-6, interleukin 6; SAA, serum amyloid A; ADA2, adenosin desaminase 2; COPA, Coat Protein Complex I Subunit Alpha; IL1RN, interleukin-1 receptor antagonist protein; IL36RN, interleukin-36 receptor antagonist protein; MEFV, mediterranean fever; MVK, mevalonate kinase; NLRC4, NLR family CARD domain containing 4; NLRP3, NLR family pyrin domain containing 3; NOD2, nucleotide binding oligomerization domain containing 2; PLCG2, phospholipase C gamma 2; TMEM173, stimulator of interferon response cGAMP interactor 1/STING1; TNFRSF1A, TNF receptor superfamily member 1A; NYHA, New York Heart Association heart failure stage; ECG, electrocardiogram; CMR, cardiac magnetic resonance imaging.

### Other amyloidosis types

Other amyloidosis types, such as Gelsolin amyloidosis, undergo system-specific examinations following the scheme for ATTRv amyloidosis. Here, individually defined further data is collected depending on the organ systems involved. Types of amyloidosis that are limited to single organs (e.g., cerebral amyloid angiopathy or Alzheimer’s disease) are not included into the registry.

### Interdisciplinary case conference

After collection of clinical data from cardiology, neurology, as well as any other potentially relevant discipline as outlined above, interdisciplinary board discussions take place in a weekly manner to collect and confirm diagnosis as well as treatment initiation and follow-up. This digital meeting allows internal as well as external physicians to present cases for interdisciplinary discussion and results in a protocol including suggestions for next steps. The protocol is added to the digital registry and communicated to the patient by the primary responsible ACCB physician, either in writing or by phone. The primary respobsible physician is assigned based on the patient’s most prominent organ manifestation. Below, the outline of the interdisciplinary protocol is depicted.

Date of conferenceParticipants: In every case conference, at least one representative of the following specialties with expertise in amyloidosis participates: Neurology, Cardiology, Hematology, Radiology (Nuclear medicine). If available or requested for special questions, representatives of Nephrology, Ophthalmology, Gastroenterology, Rheumatology and others.Case discussion:◦ Patient identifier: Pseudonym or initials/birthdate◦ Clinical context: Short depiction of most relevant symptoms and clinical findings leading to suspected diagnosis or amyloidosis or current question to be discussed.◦ Current question: Confirmation of diagnosis, therapy initiation, discussion of side effects or other reason for case presentation◦ Plan: Short summary of consented procedure including responsibilities.

Other topics to be discussed (organizational, research related etc.)

### Criteria for study discontinuation

Data collection and observation in the ACCB Registry study is terminated if the diagnosis of amyloidosis is excluded.

### Participant timelines/follow-up

Patient visits are dependent on individual disease course and underlying amyloidosis subtype. For each subtype, we predefined visit frequencies as depicted in the following sections.

### ATTRv amyloidosis follow-up

After diagnosis and staging of patients, we developed a stage-specific follow-up pattern, as described in Fig 5. The minimal core dataset for ATTRv amyloidosis follow-up includes the NIS for neuropathy and medical history/NYHA for cardiology (Fig 5, [a], NIS, in neurology; medical history and NYHA stage [a] and [b] in cardiology).

**Fig 5 pone.0350084.g005:**
[figure not shown]
Follow-up of patients with confirmed ATTRv amyloidosis at the ACCB. Left: Disease severity based on FAP stage, arrows indicate the time between follow-up visits, the charts on the right-hand side indicate the examinations planned at each follow-up visit depending on each specialty. Core datasets encompass NIS [a] for neurology and medical history/NYHA [a-b] for cardiology. NIS, neuropathy impairment score; FAP stage, family amyloid neuropathy stage; RODS, Rasch modified Overall Disability Score; 10MWT, 10 meter walk test; NCS, nerve conduction studies; EMG, electromyography, SEP, sensory evoked potentials; MRI, cranial magnetic resonance imaging; NfL, neurofilament light chain; CMR, cardiac magnetic resonance imaging; CSF, cerebrospinal fluid examination; MEP, motor evoked potentials; VEP, visual evoked potentials; GOT, aspartate aminotransferase; GPT, glutamate pyruvate alanine aminotransferase; GGT, gamma-glutamyl transferase; CBC, complete blood count; TSH, Thyroid Stimulating Hormone; IgG, immunoglobulin G; IgA, immunoglobulin A; IgM, immunoglobulin M; NTproBNP, N-terminal pro B-type natriuretic peptide; CK, creatine kinase; Vit B12, vitamin b12; Vit A, vitamin A; HbA1c, glycated hemoglobin; NfL, serum neurofilament light chains; MRI, magnetic resonance imaging; NYHA, New York Heart Association heart failure stage; ECG, electrocardiogram; CMR, cardiac magnetic resonance imaging; DPD, 99mTc-3,3-diphosphono-1,2-propanodicarboxylic acid; VUS, variant of unknown significance.

### ATTRwt amyloidosis follow-up

Since wildtype ATTR (ATTRwt) amyloidosis primarily affects the heart, follow-up visits are based on disease severity of cardiomyopathy. However, neuropathy has also been described as an increasingly prominent feature of ATTRwt amyloidosis. We therefore recommend a neurological follow-up every 12 months. Detailed examinations performed are depicted in Fig 6. The minimal core dataset for ATTRwt amyloidosis follow-up includes the NIS for neuropathy and medical history/NYHA for cardiology (Fig 6, [a] and [b] in cardiology, and [a], NIS, in neurology).

**Fig 6 pone.0350084.g006:**
[figure not shown]
Follow-up of patients with confirmed ATTRwt amyloidosis at the ACCB. Arrows indicate time between follow-up visits; charts depict examination performed at each visit depending on the specialty. Core datasets encompass medical history/NYHA [a-b] for cardiology and NIS [a] for neurology. NTproBNP, N-terminal pro B-type natriuretic peptide; GOT, aspartate aminotransferase; GPT, glutamate pyruvate alanine aminotransferase; GGT, gamma-glutamyl transferase; CBC, complete blood count; TSH, Thyroid Stimulating Hormone; IgG, immunoglobulin G; IgA, immunoglobulin A; IgM, immunoglobulin M; CK, creatine kinase; Vit B12, vitamin b12; Vit A, vitamin A; HbA1c, glycated hemoglobin; ECG, electrocardiogram; DPD scan, 99mTc-3,3-diphosphono-1,2-propanodicarboxylic acid scintigraphy; CMR, cardiac magnetic resonance imaging; NIS, neuropathy impairment score; PND score, polyneuropathy disability score; NCS, nerve conduction studies; EMG, electromyography, SEP, sensory evoked potentials; NfL, serum neurofilament light chains.

### AL amyloidosis follow up

Depending on treatment schemes, AL amyloidosis patients are followed up every 2 weeks initially, and every 3 months in stable disease, aligning with previous studies [16]. Hematological visits include collection of data on clinical symptoms, laboratory testing, and urine testing. Cardiac follow-up is performed at least every 6 months or as required, and includes clinical symptoms, ECG, echocardiography, and, if, CMR. Depending on further organ manifestations, neurological [17,18], nephrological [19], and/or gastrointestinal [20] data collections are performed as depicted in Fig 7. The minimal core dataset for AL follow-up is composed of structured medical history/NYHA (Fig 7, [a] in hematology and cardiology).

**Fig 7 pone.0350084.g007:**
[figure not shown]
Follow-up of patients with confirmed AL amyloidosis at the ACCB. Arrows indicate time between follow-up visits; charts depict examination performed at each visit depending on the specialty. Core datasets encompass medical history [a] for hematology and medical history/NYHA [a-b] for cardiology. NTproBNP, N-terminal pro B-type natriuretic peptide; GOT, aspartate aminotransferase; GPT, glutamate pyruvate alanine aminotransferase; GGT, gamma-glutamyl transferase; AP, alkaline phosphatase; CBC, complete blood count; TSH, Thyroid Stimulating Hormone; LDH, lactate dehydrogenase; IgG, immunoglobulin G; IgA, immunoglobulin A; IgM, immunoglobulin M; NYHA, New York Heart Association heart failure stage; ECG, electrocardiogram; CMR, cardiac magnetic resonance imaging.

### AA amyloidosis follow up

AA amyloidosis can have various clinical presentations and disease courses, depending on the underlying disease [14]. Follow-up is therefore generally performed on an individual basis but includes structured data collection at least yearly as shown in Fig 8. The minimal core dataset for AA amyloidosis follow-up consists of a structured medical history/NYHA (Fig 8, Medical history; [a] in cardiology).

**Fig 8 pone.0350084.g008:**
[figure not shown]
Follow-up of patients with confirmed AA amyloidosis at the ACCB. Arrows indicate time between follow-up visits; charts depict examination performed at each visit depending on the specialty. Core datasets encompass medical history for therapy of underlying disease, and medical history/NYHA [a-b] for cardiology. UACR, urine albumin-creatinine ratio; UPCR, urine protein creatinine ratio; CRP, C-reactive protein; PCT, procalcitonin, anti-IL-1, anti-interleukin 1; anti-IL6, anti-interleukin 6 SAA, serum amyloid A; NYHA, New York Heart Association heart failure stage; ECG, electrocardiogram, CMR, cardiac magnetic resonance imaging.

### Data collection and management

After patient selection and written informed consent, upon registration in our research database (Tbase), each participant is assigned an ongoing number as pseudonymization code. Data is stored using the digital interoperable Tbase platform developed in the clinic as part of research efforts. Keys for patient re-identification is stored within the Tbase platform only accessible by the research personal. The Tbase research database is located within the secure environment of Charité – Universitätsmedizin Berlin, featuring encryption during transmission and storage, role-based access control, and audit logs.

To collect patient reported outcomes (PROMs) more efficiently, a patient facing smartphone application called dotbase (a digital medical workspace designed for clinical environments, dotbase medical GmbH, Berlin, Germany. Available at: https://dotbase.org) is used, allowing collection of questionnaires from outside of the clinic. Third-party digital tools (dotbase, Tbase) are based on specific collaboration agreements and technology is hosted in Germany. Data access is completely restricted to and hosted by Charité – Universitätsmedizin Berlin. All data access is logged and changes are trackable. Patient recruitment, data flow and distribution are visualised in Fig 9. During clinical visits, physicians directly input data into the electronic database (Tbase). Here, data from the electronic health record (EHR), e.g., laboratory results, imaging, and functional examinations, are included automatically. Data items were selected according to clinical relevance and agreed upon core data sets. The resulting information is combined with patient reported outcomes and additional information such as type of referring physician or date of earliest symptoms.

**Fig 9 pone.0350084.g009:**
[figure not shown]
Data flow and technical infrastructure at ACCB. The left side depicts data collection by the physician at study visits or by the patient, and data flow to the relational database (grey box in the middle), which integrates data from the dotbase platform into the tbase platform. The right side depicts data use either by the local researcher or data sharing via the interoperable FHIR format. EHR, electronic health record; FHIR, Fast Healthcare Interoperability Resources; DAC, Data Access Committee.

Data stored in this system can be extracted into tabular format by researchers and physicians via standardised interfaces into common analysis software. Additionally, data can be extracted in the Fast Healthcare Interoperability Resources (FHIR) format [21], or in the form of Human phenotype ontology (HPO) [22] codes [22] per patient. Encoding information in FHIR format allows for quick interoperability with other disease registries. Most data items that are collected inside the registry software are additionally connected to HPO definitions. For each patient, a list of HPO codes, including time domain information, that describes the phenotype and clinical presentation in a standardised way, including ORPHAcodes, can be created. Data sharing is governed by a Data Access Committee (DAC). The DAC consists of the clinical lead (principal investigator), a statistician, and a member of the Ethics board upon request. Internal data access is role based (Role Based Access Control, RBAC). External data access can be requested via email to [contact] and is evaluated by the DAC regarding scientific merit, feasibility, and privacy safeguards. Quality control and periodic data audits are performed bi-yearly and include range checks, detection of duplications, and revision of inter-rater reliability.

We furthermore plan to create an automated connection between the registry database and the data integration center (DIZ) of the university medical center, establishing a direct link between the existing data sharing infrastructure of German university hospitals, as part of the “Netzwerk Universitätsmedizin” (NUM) initiative [23]. This will make data gathered in this registry available to other researchers using the “Forschungsdatenportal Gesundheit” (FDPG) online portal [24], for data privacy ensuring decentralised analysis.

### Biobanking

For biobanking, serum and EDTA blood samples are collected at the first visit, as well as every 12 months. Serum samples are centrifuged at 2,500 g for 10 minutes, both serum and EDTA are distributed into 250µl aliquots and stored at −80°C at the Central Biobank (ZeBanC) for up to 30 years post study inclusion. Additionally, any tissue biopsies taken are stored at the ZeBanC after written informed consent. Access to biospecimen by written request has to be individually granted by the principal investigator. Sample destruction in case of participant withdrawal is performed upon written instruction by the study team.

### Statistical analysis plan

We prespecify the following primary endpoints: [1] overall survival from registry enrolment; [2] organ-specific progression (e.g., incident heart failure, renal failure) defined by laboratory, imaging, and electrophysiological standard clinical criteria (e.g., N-terminal pro B-type natriuretic peptide or reduction of ejection fraction in echocardiography for heart failure, creatinine clearance for renal failure, neurofilament light chains and nerve conduction studies for neuropathy progression, and further as detailed in the subtype-specific sections in the Study Protocol); and [3] longitudinal quality-of-life scores. Secondary endpoints include subtype-specific trajectories and treatment-specific outcomes. Survival endpoints will be calculated using Kaplan–Meier and Cox models; when competing risks are relevant (e.g., cause-specific events), Fine–Gray models will be used. Longitudinal continuous outcomes (biomarkers, PROMs) will be analysed with linear mixed-effects or generalised estimating equations. For comparative effectiveness questions, we will adjust for confounding using multivariable regression and propensity score methods (matching/weighting); the a priori covariate set includes age, sex, subtype, baseline stage/organ involvement, and key comorbidities (DAG-informed).

Missing data will be addressed by multiple imputation by chained equations (MICE) under a MAR assumption; results will be pooled with Rubin’s rules and compared with complete-case analyses in sensitivity checks. We control multiplicity for primary endpoints (e.g., Holm/Bonferroni) with α = 0.05 (two-sided). Interim analyses are descriptive only. Based on current referral volumes, we anticipate enrolment of ~20–30 patients/year; over five years (N ≈ 100–150), precision for a 10% event rate is ±~6% (95% CI). Analyses will be performed in R; code and analysis manifests will be shared with the de-identified data release. To address time-dependent exposures, treatment status will be modelled as a time-varying covariate using episode splitting, in which each patient’s follow-up is partitioned into consecutive intervals reflecting their actual exposure status at each point in time. Immortal-time bias will be addressed by classifying all person-time prior to treatment initiation as unexposed, ensuring that the pre-treatment observation window is not misattributed to the treated state. Since treatment switches most commonly occurr in the context of clinical progression, they will be handled by opening a new interval at the date of the switch, with exposure updated accordingly to reflect the new treatment, while prior intervals retain their original classification. Treatment discontinuation will be handled analogously, with patients reclassified as unexposed from the discontinuation date onward. Where dose-level data are available, dose changes will be treated by the same mechanism.

We acknowledge two limitations inherent to a routine-care registry setting. First, treatment event dates are recorded at clinical visits rather than to the exact calendar day; interval boundaries therefore carry a degree of temporal imprecision. Second, the frequency and timing of follow-up visits are clinically driven rather than protocol-fixed, which may result in treatment changes between visits not being captured with full precision. To quantify the potential impact of the first limitation, a sensitivity analysis applying a ± 4-week uncertainty window around documented treatment event dates will be conducted. As a further sensitivity analysis, a landmark approach will be applied at 6 and 12 months, classifying patients by treatment status at the landmark and restricting follow-up accordingly; as this approach avoids immortal-time bias by design rather than by statistical adjustment, convergence of results with the primary analysis will serve as an indicator of robustness. Given these constraints, comparative effectiveness estimates derived from time-dependent Cox proportional hazards models should be interpreted as exploratory and hypothesis-generating rather than causal.

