**Methods:**

This is a single-center prospective registry study that enrols patients diagnosed with systemic amyloidosis. The registry includes demographic data, multidisciplinary clinical phenotyping, biomarkers, biobanking, genetic information, imaging studies, and patient reported outcomes. Here, we describe the standardised protocol for diagnostic workup, baseline and longitudinal data collection, and disease-specific follow-up algorithms. Data will be collected digitally in interoperable data formats to ensure shareability in accordance with GDPR-policies.

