### Eligibility criteria

#### Inclusion criteria.

1. Age ≥ 18 years2. Patients with suspected or diagnosed amyloidosis (any of the below)a. Clinically suspected diagnosis resulting from imaging or laboratory parametersb. Histomorphological diagnosis of amyloidosis or positive DPD scanc. Genetically confirmed TTR mutation3. Voluntary signing of informed consent (including opt-in options for collection of biological specimens)

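### Primary overall survival is timed from enrolment, but patients can enrol before amyloidosis is confirmed, or on a TTR mutation alone, and leave observation if it is excluded

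*Protocol article*

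**What the plan says.** The section 'Statistical analysis plan' prespecifies "overall survival from registry enrolment" as the first primary endpoint and adds: "Survival endpoints will be calculated using Kaplan–Meier and Cox models". It names no analysis set for this endpoint. Subtype-specific trajectories are secondary endpoints; subtype otherwise appears there in the covariate set for comparative effectiveness.

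Other sections determine who is in the cohort and for how long:

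- **Inclusion criteria.** The clinical criterion reads "Patients with suspected or diagnosed amyloidosis (any of the below"), so one item is enough. The items include "Clinically suspected diagnosis resulting from imaging or laboratory" parameters and, separately, "Genetically confirmed TTR mutation". Neither requires manifest, confirmed disease.
- **Study setting.** Patients come from the centre's own clinic and from referring physicians, with suspected or already confirmed disease. Suspected cases are observed until amyloidosis is ruled out. A case conference either confirms the diagnosis or orders further tests and another conference.
- **Study Protocol and Interdisciplinary case conference.** Consent and enrolment take place in cardiology and neurology, where a possibly still suspected diagnosis is recorded. The conference that confirms the diagnosis follows data collection.
- **Criteria for study discontinuation.** Data collection is "terminated if the diagnosis of amyloidosis is excluded".
- **Abstract, Methods.** The registry "enrols patients diagnosed with systemic amyloidosis", which is narrower than the inclusion criteria.

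**The concern.** A survival curve needs a population, a starting time and a reason for leaving that is unrelated to prognosis. Here the starting time is fixed at enrolment, but at that moment it may not be known whether the patient has the disease. Two analyses are compatible with the text.

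1. **All enrolled.** Suspected patients who turn out not to have amyloidosis count in the risk set during work-up and are then censored because of their disease status. That censoring is informative. Carriers without disease stay at risk and add low-mortality person-time.
2. **Confirmed cases only, from enrolment.** A patient who enrols on suspicion must survive the work-up to be counted. The interval from enrolment to confirmation is then immortal, and a death within it drops out of the analysis.

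At stake is the first primary endpoint of a registry that aims to describe the real-world course of the disease and support risk stratification. A pooled survival figure that moves with the share of suspected cases and carriers is hard to interpret or to compare with other cohorts. More recruitment narrows its interval without removing the problem.

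**Working it through.** The plan gives no survival figure, hazard or case mix. Every hazard, share and duration below is an assumption used to show scale.

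**A. Confirmed cases only, timed from enrolment**

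Assume a constant hazard of 0.36 per year, a work-up of length w of 1 or 3 months, and a share f of patients entering as suspected. Patients who die before confirmation are dropped.

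- True 1-year survival: exp(−0.36) = 0.6977.
- Reported 1-year survival: 0.6977 / [(1 − f) + f·exp(−0.36·w)], where exp(−0.36·1/12) = exp(−0.03) = 0.9704 and exp(−0.36·3/12) = exp(−0.09) = 0.9139.

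| Share entering as suspected | w = 1 month | w = 3 months | Overstatement (points) |
|---|---|---|---|
| 30% | 0.7039 | 0.7162 | 0.6 to 1.8 |
| 50% | 0.7081 | 0.7291 | 1.0 to 3.1 |
| 100% | 0.7189 | 0.7634 | 2.1 to 6.6 |

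Of those entering as suspected, 1 − 0.9704 = 3.0% to 1 − 0.9139 = 8.6% die before confirmation and disappear. The last row is an upper bound, because confirmed cases are also referred in.

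**B. Carriers pooled with disease**

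Assume mortality of 15% per year with disease and 1% per year in carriers without disease, with carriers making up a share c. Pooled 5-year survival is c·exp(−0.05) + (1 − c)·exp(−0.75), with exp(−0.05) = 0.951 and exp(−0.75) = 0.472.

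- c = 0: 0.472
- c = 10%: 0.520
- c = 20%: 0.568
- c = 30%: 0.616

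**C. All enrolled, with exit on exclusion**

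Assume hazards of 0.20 per year with disease, 0.01 in carriers and 0.04 in suspected patients without disease, who leave after a mean of 0.25 years. Three-year survival with disease is exp(−0.6) = 0.549. Simulating 400,000 patients per mix gives these 3-year values; direct integration of the pooled hazard agrees to within about 0.001.

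| Confirmed / carriers / suspected (share of suspected truly diseased) | Kaplan–Meier, all enrolled | Actual survival, all enrolled | Patients with amyloidosis |
|---|---|---|---|
| 80/10/10 (50%) | 0.594 | 0.607 | 0.549 |
| 60/10/30 (50%) | 0.603 | 0.642 | 0.549 |
| 50/20/30 (50%) | 0.651 | 0.684 | 0.549 |
| 40/20/40 (30%) | 0.672 | 0.728 | 0.549 |
| 60/0/40 (30%) | 0.556 | 0.643 | 0.549 |
| 60/40/0 | 0.717 | 0.717 | 0.549 |

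In the first four mixes, which contain both groups, the curve lies about 4.5 to 12.3 points above survival with amyloidosis and about 1.3 to 5.6 points below actual survival of everyone enrolled. The last two rows separate the causes. Without carriers, the curve is close to survival with amyloidosis (0.7 points above). Without suspected cases, it matches the enrolled cohort. Under these assumptions, carriers produce the gap to the diseased group, and exit on exclusion produces the gap to the enrolled group.

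**The case against.** The strongest reply is that this is a missing definition. An article condenses a full protocol, and analysis sets are commonly left to that document or to a separate SAP. The Objectives and Study Protocol sections speak of people diagnosed with or affected by systemic amyloidosis, which hints at a confirmed set. The discontinuation rule does not say that excluded patients remain in the survival set as censored. This has weight, but it does not settle the matter. The article itself fixes the origin at enrolment, and restricting the set to confirmed cases while keeping that origin creates the immortal time in part A. The plan handles immortal time carefully for treatment start but does not mention it for confirmation of diagnosis.

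A reader might also infer several stronger points that the documents do not support:

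- **That the curve describes no definable population.** The enrolled cohort can be listed, and enrolment is a legitimate origin that avoids crediting survival before entry.
- **That the estimate is biased upward under every reading.** The late entry of patients with an existing diagnosis can act in either direction. With an assumed hazard of 0.4 per year in year 1 and 0.1 after, 3-year survival from enrolment is 0.55 for new cases and 0.74 for those entering two years after diagnosis. With a constant hazard the two are equal, and with a rising hazard the order would reverse. The documents give no hazard shape. Mortality of excluded suspected cases is also not given.
- **That carriers of variants of unknown significance are pooled into survival as if their variant were pathogenic.** The baseline section for ATTR amyloidosis says only that they have the same examinations.
- **That carriers are a large share.** The criterion admits them, but the article gives no number, and the ATTRv follow-up scheme is for confirmed disease. If the discontinuation rule were applied to carriers without disease, the dilution would be smaller.

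The mismatch in the abstract is editorial: the body consistently includes suspected cases.

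**Conclusion.** The point holds in this form. The stated origin, entry criteria and stopping rule do not combine into a clean primary survival estimate. An analysis of all enrolled targets neither the enrolled nor the diseased group once both suspected cases and carriers are present. An analysis of confirmed cases from enrolment builds in immortal time.

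The size is uncertain. On the assumed 0.36 per year and a 1 to 3 month work-up, the immortal-time effect on 1-year survival is about 0.6 to 1.8 points if 30% enter as suspected, with an upper bound of 2.1 to 6.6 points if all do. Carrier dilution could be larger, from 47% to 52–62% at 5 years, but only if carriers really form 10–30% of the cohort and mortality is 1% against 15% per year. The mechanism follows from the text; the magnitudes do not.

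This should be fixed before the survival analysis is run. It is not a fatal flaw in an observational registry whose other objectives do not depend on this curve.

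**What to change.** Amend the endpoint definition as follows:

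1. Define the primary overall survival set as confirmed systemic amyloidosis, with risk time starting at the later of enrolment and confirmation.
2. Report survival by subtype alongside any pooled curve. Stratifying the Cox baseline hazard by subtype is a reasonable option, not a required correction.
3. Report disease-free carriers of TTR mutations or variants of unknown significance separately.
4. Show in the flow diagram how many suspected cases were excluded and how many died before confirmation, since the primary curve will not contain those deaths.
5. Align the abstract with the inclusion criteria.
6. Where the original diagnosis date is available, add a sensitivity analysis with origin at diagnosis and delayed entry, or adjust for time since diagnosis.

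Items 1 to 5 are mainly wording: conference protocols carry a date and are already added to the registry. They cost a small amount of early person-time. Item 6 is less certain. The conference record supplies the local date, and the article does not show that the original diagnosis date is held for patients referred already confirmed. Delayed entry also leaves small early risk sets and unstable early estimates, most of all in a subtype with high early mortality, so it is better kept as a sensitivity analysis.
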